## 2. Methods

### 2.1. Study Design

The PACO study is a randomized controlled trial setting in public high schools from three Spanish cities (Granada, Jaén, and Valencia), where the schools are the units of randomization, and individuals within the schools are the units of analysis (the participants). The intervention focuses on promoting cycling to school and will be implemented in adolescents during 1 month within the physical education (PE) curriculum classes. Six high schools (i.e., an intervention and a control school in each of the 3 involved cities) will be randomly selected to participate. All study participants will be assessed before and after the intervention period using assessment procedures described below.

The PACO study has been approved by the Review Committee for Research Involving Human Subjects at the University of Granada (Reference: 162/CEIH/2016) and registered with a ClinicalTrials.gov ID: NCT03937336. In addition, the present study protocol has been written in accordance with the Standard Protocol Items: Recommendations for Interventional Trials (SPIRIT) statement (see supplementary file 1).

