### 2.2. Study Population

A total of 360 adolescents aged 14–15 years (3rd grade of secondary education; hereinafter called 3rd grade) from 6 high schools located in 3 Spanish cities will be recruited (see Figure 2). The randomization process is presented in the Figure 2. Within each city, 2 high schools, randomly selected and allocated to intervention or control treatment, will participate in the study. Within each secondary school, two class groups of approximately 30 participants each will be invited to participate and allocated to intervention or control conditions. The final target sample will comprise 360 adolescents (120 adolescents per city; 180 adolescents in the intervention and 180 in the control group).

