#### 2.3.3. Sample Size Calculations

A minimum sample size of 300 participants will be needed to detect an odds ratio of 1.5 in the primary outcome (i.e., PA), assuming an alpha error of 0.05 and 80% of statistical power [51]. Therefore, 50 participants regardless of gender per school (6 schools) are needed. To account for the potential loss to follow-up of up to 50% participants regardless of gender (based on investigators’ previous experience due to the use of wearable devices), a total of 360 adolescents will be recruited (i.e., 120 participants per city). The groups randomization will be done at a 1:1 ratio at city level (i.e., from each city, 60 participants will be randomized to intervention and 60 to control groups).

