## 6. Data Analysis

Descriptive characteristics of the sample will be reported as means and standard deviations for continuous variables, and frequencies and percentages for categorical variables. Analysis of variance and Chi-square tests will be conducted to determine differences in all variables between study group (i.e., control or intervention) at baseline.

Firstly, the appropriateness of the randomization process will be analysed by exploring outlier values and the normal distribution of the variables using the Kolgomorov–Smirnov test and graphical procedures (normal distribution plots). After inspecting outliers and extreme values, these will be winsorized using the 1st percentile and 99th percentile of the distribution of variables.

Secondly, analysis of covariance (ANCOVA) will be used to analyse the main effects of the study group (fixed factor) on cycling to school, ACS, PA levels, SDT-related variables in ACS, and individual, interpersonal, and environment variables related to ACS from the SEM (dependent variables). The effect size between groups will be calculated according to Lipsey and Wilson (2001), with the following formula: r = [t^2^/(t^2^ + gl)], where t = value of the Student t statistic and gl = degrees of freedom. Additionally, to examine change between baseline and post-intervention, regression models will be used, including the study group in the model as fixed factor and the mean difference (post-intervention minus baseline) of outcome variables as dependent variable.

Finally, to analyse the influence of covariates in the association of the intervention and the main outcome (i.e., cycling to school, ACS, and PA levels), mediation analyses will be performed using the PROCESS macro for SPSS (SPSS Inc., Chicago, IL, USA). For these analyses, the intervention will be included as independent variable and main outcomes as dependent (i.e., cycling to school, ACS and PA levels). Mediators that will be analysed are cycling knowledge, cycling skills, basic psychological needs satisfaction in ACS, motivation for ACS, barriers to ACS from adolescents and parents, and peer social support for ACS.

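### Six schools are randomised, but the stated ANCOVA, change-score regression and mediation models work at pupil level with no valid allowance for school, so their p-values are too small whenever the baseline value leaves school effects behind

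*Protocol article*

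**What the plan says.** Section 2.1 fixes the design: "Six high schools (i.e., an intervention and a control school in each of the 3 involved cities) will be randomly selected to participate", and "the schools are the units of randomization, and individuals within the schools are the units of analysis". Section 2.2 puts about 60 pupils in each school: "two class groups of approximately 30 participants each will be invited to participate". Section 2.3.3 asks for 300 pupils ("50 participants regardless of gender per school (6 schools) are needed") and mentions no ICC or design effect. It then describes allocation as if pupils were the unit: "from each city, 60 participants will be randomized to intervention and 60 to control groups".

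For the main effects, section 6 states that "analysis of covariance (ANCOVA) will be used to analyse the main effects of the study group (fixed factor"). It adds a regression of the post-minus-baseline difference on study group, and mediation models in the PROCESS macro. The covariate list for the regression models, later in section 6, includes school name and class. It also includes enrolment, school socioeconomic status, school engagement, population density, city income, cycle-lane length, bicycle racks and weather. The limitations in section 7 mention the small sample but not clustering.

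**The concern.** Only six units are allocated at random, so the evidence for an intervention effect is the contrast between three school averages and three others. A pupil-level test measures its error from variation among pupils and uses several hundred degrees of freedom. It therefore treats differences between schools as if they were almost free of chance.

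The article itself expects schools to differ. Section 4.2.2 measures cycle lanes, racks and weather by school and records engagement because it may influence the effect. Section 7 lets teachers choose the participating classes. If such differences change between the two waves, or are only partly removed by baseline adjustment, some of them will be declared intervention effects at more than the nominal rate.

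**Working it through.** **Inputs.** From the article: 6 schools, 3 per arm; m = 60 pupils per school (section 2.2), or 30 if the 50% loss allowed for in section 2.3.3 occurs; alpha 0.05 (two-sided assumed). Assumed: ICC 0.01 to 0.10, since none is given.

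**The plan's own figure.** There is none for clustering. The required 300 is 6 × 50 with no design effect. (It also does not reproduce as a two-group comparison for an odds ratio of 1.5: two-sided, at least 384 per arm are needed at every control rate tried from 5% to 60%. That is a separate matter.)

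**1. Pupil-level test without baseline adjustment.** Design effect DE = 1 + (m − 1) × ICC; true type I error = 2 × [1 − Φ(1.96/√DE)].

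| ICC | DE, m = 60 | Type I error | DE, m = 30 | Type I error |
|---|---|---|---|---|
| 0.01 | 1.59 | 12% | 1.29 | 8% |
| 0.02 | 2.18 | 18% | 1.58 | 12% |
| 0.05 | 3.95 | 32% | 2.45 | 21% |
| 0.10 | 6.90 | 46% | 3.90 | 32% |

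Simulation (20,000 runs, m = 60) gave 12%, 18%, 33% and 47%. Tests on school means held about 5%.

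**2. ANCOVA with school effects identical at both waves.** ANCOVA subtracts b × baseline with b below 1, so a fraction (1 − b) of each school effect remains. Take unit variance at each wave and assume a within-school pupil correlation of 0.6 between waves (not in the article). Then b = ICC + 0.6(1 − ICC), residual school variance = ICC(1 − b)², and residual pupil variance = (1 − ICC)(1 + b² − 1.2b).
- ICC 0.01: b = 0.604; variances 0.00157 and 0.634; residual ICC 0.0025; DE = 1 + 59 × 0.0025 = 1.15; error about 7%.
- ICC 0.10: b = 0.640; variances 0.0130 and 0.577; residual ICC 0.022; DE = 1 + 59 × 0.022 = 2.30; error about 20%.

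This agrees with the simulated range of about 6% to 21%. If the school effects correlate only 0.5 between waves, simulated ANCOVA error is about 14% to 47%.

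**3. Change score.** A stable school effect cancels exactly, and simulated error was 5% to 6% at every ICC. At a between-wave school correlation of 0.9 it was 6% to 23%. At 0.5 it matched or exceeded the figures in step 1.

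**4. Rare cycling.** Section 1.1 gives 0.3% and under 2% for cycling to school. Simulated beta-binomial outcomes, ICC 0.01, 0.02, 0.05, 0.10:
- 0.3% cycling, m = 60: 2.1%, 4.3%, 7.2%, 8.4%. With m = 30: 0.4% to 4.0%.
- 2% cycling: 10% to 35% (m = 60) and 6% to 19% (m = 30).

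**5. School name and class as covariates.** Each school belongs to one arm. Intercept, study group and five school indicators make 7 columns of rank 6, so the group effect is aliased with schools. Class indicators, nested in school, do the same.

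**6. School- and city-level covariates.** Six schools less intercept and group leave 6 − 2 = 4 degrees of freedom. The list has seven such covariates before weather. City indicators alone do not repair the test: simulated error with them was 13.7% at ICC 0.01 and 32.4% at 0.05.

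**7. What the design supports.** The planned pupil-level test has about 6 × 60 − 2 = 358 degrees of freedom (critical t 1.97). Three schools against three give 4 (critical t 2.78), or 2 if paired by city (4.30). Permuting within three city pairs cannot give a two-sided p below 2/2³ = 0.25.

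**The case against.** A reader might infer that every p-value and confidence interval in the trial will be too optimistic, or that 12% to 47% applies to each planned analysis. The documents do not support that. The size depends on an ICC and a between-wave stability that they do not give. Cycle lanes and routes change little in a month, and stable differences cancel in the change score. At 0.3% cycling, the pupil-level test is below its nominal level at the lower ICCs. The article does not mention confidence intervals at all. This part of the objection stands and limits the claim.

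Three further defences do not rescue the plan:
- Individuals can properly be the unit of analysis in a cluster trial. That is true, and the sentence in section 2.1 is not itself the fault. It needs a model that carries the school, and section 6 names none.
- School name and class are covariates. In those regressions the fault is an inestimable effect, not an optimistic p-value, and the list says nothing that repairs the ANCOVA.
- A separate analysis plan could supply the detail. But the article states the unit, models, covariates, software and significance level, so a wrong choice has been stated.

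Sections 2.2 and 2.3.3 blur the allocation unit, but section 2.1 is explicit, and allocation by class would still be cluster allocation.

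**Conclusion.** The point holds with conditions. The stated tests give p-values that are too small whenever school effects remain after the baseline value is taken into account. For a continuous or common binary outcome with 60 pupils per school and an assumed ICC of 0.01 to 0.10, the nominal 5% is about 12% to 47% unadjusted. For ANCOVA it is about 6% to 21% under fully stable school effects, which is the most favourable case for that model. The change-score regression is affected only if school effects shift between waves, and cycling at 0.3% is little affected or not at all. As listed, the covariate-adjusted regressions cannot estimate the group effect. The ICC, the stability of school effects and the pupils' own correlation between waves are all assumptions. The nesting of schools in arms is not. The plan should be corrected before analysis.

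**What to change.** - **Primary analysis.** Adjust pupil outcomes for baseline and pupil-level covariates only, average by school, and compare three schools with three by t on 4 degrees of freedom. Give a city-paired version on 2 as sensitivity. Alternatively, use a mixed model with random school intercept and Satterthwaite or Kenward-Roger degrees of freedom; large-sample inference is not adequate with three schools per arm.
- **Binary commuting outcomes.** Analyse school proportions, or use a model suited to binary data.
- **Covariates.** Remove school name, class and all school- and city-level covariates from the effect models.
- **Reporting.** Give the ICC and the estimate with its interval. State that six schools support estimation, not a confirmatory 5% test.
- **Mediation.** Label it exploratory unless school is accounted for.
- **Wording.** Correct the statement in section 2.3.3 that participants are randomised.

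**Cost.** No new data are needed. For an unadjusted comparison with 60 per school, intervals widen by √DE × 2.776/1.96: about 1.8 times at ICC 0.01 and 3.7 times at 0.10. Power is low. For the stated odds ratio of 1.5, with a control rate of 100 − 76.6 = 23.4% (a background figure in section 1.1, not a stated design input), the school-level test has about 18%, 15% and 10% power at ICC 0.01, 0.02 and 0.05. Only more schools would change that materially.

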### 2.2. Study Population

A total of 360 adolescents aged 14–15 years (3rd grade of secondary education; hereinafter called 3rd grade) from 6 high schools located in 3 Spanish cities will be recruited (see Figure 2). The randomization process is presented in the Figure 2. Within each city, 2 high schools, randomly selected and allocated to intervention or control treatment, will participate in the study. Within each secondary school, two class groups of approximately 30 participants each will be invited to participate and allocated to intervention or control conditions. The final target sample will comprise 360 adolescents (120 adolescents per city; 180 adolescents in the intervention and 180 in the control group).

### 2.3. Procedure

#### 2.3.1. School Recruitment and Randomization

A list of all public high schools from each of the participating cities will be obtained from the educational government institutions (see Figure 3). The schools will be randomly selected in each city separately and a final ordered list will be created. The inclusion criteria for schools´ participation will be: (1) the school must have at least 2 class groups of 3rd grade of secondary education, (2) each class group must include at least 15 adolescents, (3) there must be at least 15 informed consents per class group, (4) the adolescents must have not taken part in other interventions to promote ACS or PA during the PACO study intervention period, and (5) the school must not offer bus transportation to the adolescents. If a school decides not to participate in the study, the same procedure will be carried out with the next selected school from the ordered list.

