The perceived barriers to allow their children to commute actively to school will be assessed using the previous valid and reliable PABACS (Parental Perception of Barriers towards Active Commuting to School) questionnaire in Spanish children and adolescents [68]. It is a 23-item questionnaire categorized into 3 scales (general, walking, and cycling barriers) designed to determine the main parental barriers. The final variable to analyse will be an average score ranging from 1 to 4 (strongly disagree to strongly agree), for every item and for every scale.

(8) Peer social support

The peer social support to ACS will be self-reported by parents using a question from the School Travel and Safety survey used in the “Walk to School” study among American children [5]. The question will be: *“How often do other people in the neighbourhood walk or cycling with children to/from school?”* Response options: *everyday, a few times a week, a few times a month, a few times a year, or never*. The final variable to analyse will be the percentage of parents at a given school who will respond “everyday” or “a few times a week”.

(9) School characteristics

The student enrolment will be a measure of the school size (i.e., the number of students enrolled in the school during the year of participating in the current study). The school socioeconomic status will be calculated in accordance to previous studies [77,78]. Then, school neighbourhoods will be objectively analysed and classified as high or low socioeconomic status based on a Geographic Information System. The school engagement (to define its implication within the study since it might influence the intervention effects obtained in the study) will be 3 study reporting 3 variables per school: “teacher’s engagement” (i.e., the average of the researcher staff perceptions of the teacher’s engagement from all the classes); “student’s engagement” (i.e., the average of the researcher staff perceptions of the student’s engagement from all the classes); and “school’s engagement” (i.e., the average of the previous teachers and student’s engagement).

(10) City characteristics

The population density (number of inhabitants per city area in km^2^ -inhabitants/km^2^-) will be obtained from the Ministry of Finance and Public Administration of Spain, using the available data closest to the data collection year in each city. The city income from the data collection year will be obtained from the Spanish Public Tax Agency.

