The following covariables will be included in the regression models: children´s age and gender, date of birth, school grade and name, class, bicycle ownership, parent´s age and gender, weight, height, waist circumference, body mass index, family income, parental educational level, student enrolment, school socioeconomic status, school engagement, population density, city income, distance home-school, cycling lane length, bicycle racks and weather.

Considering that our main aim is to assess real-world effectiveness of the intervention, we will conduct a primary analysis based on an intention-to-treat principle (in which we will analyse participants according to the groups originally assigned). Then, we will conduct a sensitivity analysis per protocol (in which we will exclude participants who did not complete the intervention and/or did not reach a minimum of 75% of attendance).

Analyses will be conducted using the Statistical Package for Social Sciences (SPSS, v. 25.0, IBM SPSS Statistics, IBM Corporation), and the level of significance will be set at *p* < 0.05.

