In the search for balance, several pragmatic adaptations will be made to conduct the research in “real-world” scenarios (such as school) where decisions need to be made on how to best conduct the study with the limited amount of time and resources that researchers may have [82]. In the PACO study, these adaptations pertain to the study design, implementation, and evaluation. Firstly, the school teachers will be able to choose the participating class groups, within the same grade. The pilot study and several consultations with school teachers showed that teachers want to choose the participating class and this will increase their involvement in the intervention. Secondly, all high schools in the three participating cities will be included in the random selection processes and then, the chosen schools will be invited to participate. Time limitations do not allow to visit each school for this purpose, and emails to schools have been previously sent (in previous studies of the research group) and they have not been answered because of high workload. Consequently, we will include all the schools in the random process to guarantee that everyone has the same likelihood to be selected. Thirdly, the intervention includes 4 sessions during a 1-month period. Research staff will offer the option to teachers of spreading the 2 h lesson of the 2nd and 4th session in two 1 h sessions using the normal PE schedule. In Spain, the national educational system in secondary schools mandates 2 h per week of PE. Fourthly, regarding the organization of the academic year in 3 trimesters, the study will be implemented in full trimesters to avoid holiday times, including the assessments. Finally, the cycling skills will be assessed by the teacher using a checklist twice during the intervention, simulating real evaluation conditions. However, safety (e.g., to avoid risky activities where children perform skills that they have not learned yet) and time limitations (e.g., lack of more PE sessions to enlarge the intervention), will prevent the cycling skills assessment being carried out at baseline and follow-up, respectively. To summarize, doing research in schools is important to prevent unhealthy behaviours and related beliefs common in our society. Achieving a balance between the scientific requirements of randomized designs and the constraints imposed by real world circumstances is necessary to improve the quality of research conducted in educational settings [83]. It is also consistent with recent calls to achieve a balance between the established evidence-based pathway and a practice-based evidence pathway, and for a more nuanced approach to appraising the utility of diverse types of evidence [84].

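### School pairs are balanced on city alone, so with three schools per arm the planned GIS socioeconomic class will probably be unequal between arms, and six schools cannot adjust for it reliably

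*Protocol article*

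**What the plan says.** All references are to the Protocol article.

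- Section 2.1: "Six high schools (i.e., an intervention and a control school in each of the 3 involved cities) will be randomly selected to participate". Schools are randomised, while "individuals within the schools are the units of analysis".
- Section 2.2: "Within each city, 2 high schools, randomly selected and allocated to intervention or control treatment, will participate in the study".
- Section 2.3.1: "The schools will be randomly selected in each city separately and a final ordered list will be created". A school that declines is replaced by the one after it on that list, whatever its type.
- Section 7 confirms that the draw is unrestricted: "we will include all the schools in the random process to guarantee that everyone has the same likelihood to be selected".
- Section 4.2.2, item 9: "school neighbourhoods will be objectively analysed and classified as high or low socioeconomic status based on a Geographic Information System".
- Section 6 uses that class only as one regression covariate among many, in a list that ends "student enrolment, school socioeconomic status, school engagement, population density, city income, distance home-school, cycling lane length, bicycle racks and weather". The same list includes school name, and also family income and parental education.

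No part of the text matches, stratifies or constrains the draw or the allocation on anything except city.

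**The concern.** The plan regards school SES as relevant: it appears in Table 1 among the factors related to active commuting to school (ACS), and again as a covariate in section 6. It is a fixed property of the school's neighbourhood, and the list of public schools is in hand before any school is approached. It could therefore be used when each city's pair is formed, but is used only in the analysis.

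With three schools per arm, a single city in which a high-SES school faces a low-SES school can shift the balance of the whole trial. If SES affects how pupils respond to the cycling sessions, or how their commuting or activity drifts over the month, that difference enters the comparison of arms. The planned remedy, regression adjustment, has little between-school information to work with.

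**Working it through.** **Inputs from the protocol.** Three cities, one intervention and one control school in each (sections 2.1, 2.2); draw and allocation random within city; SES in two classes (section 4.2.2). The plan states no figure for expected balance, so there is none to reproduce.

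**Assumed input.** The share *p* of schools classed as high SES is not given. I use 0.2 to 0.5; results are symmetric, so this covers 0.2 to 0.8.

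**Step 1: chance that the arms differ.** The number of high-SES schools in each arm is Binomial(3, *p*), so

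P(differ) = 1 − Σₖ [C(3,k) pᵏ (1−p)³⁻ᵏ]².

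- *p* = 0.5: the terms are 1/8, 3/8, 3/8, 1/8. Their squares sum to 20/64, so P(differ) = 44/64 = 0.69.
- *p* = 0.2: the terms are 0.512, 0.384, 0.096, 0.008. Their squares sum to 0.419, so P(differ) = 0.58.

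| p | counts differ | differ by 2 or 3 schools | at least one city pair discordant |
|---|---|---|---|
| 0.1 | 0.41 | 0.04 | 0.45 |
| 0.2 | 0.58 | 0.11 | 0.69 |
| 0.3 | 0.65 | 0.17 | 0.81 |
| 0.5 | 0.69 | 0.22 | 0.88 |

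The last column is 1 − [1 − 2p(1−p)]³. The first probability falls below one half only when *p* is under about 0.15 or over about 0.85. Drawing from a short finite list changes little: with half the schools high SES, it is 0.72 for 6 schools per city and 0.69 for 40.

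**Step 2: what the imbalance does to a contrast.** Let *g* be the high-minus-low difference in whatever quantity is compared. Chance imbalance adds an error with mean 0 and SD = g·√(2p(1−p)/3), which is 0.41g at *p* = 0.5 and 0.33g at *p* = 0.2. The protocol gives no value for *g*. Two illustrations at *p* = 0.5, both on assumed inputs:

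- Unadjusted difference in post-intervention level, *g* = 10 percentage points of ACS: SD 4.1 points.
- Difference in one-month change, *g* = 0 to 2 points: SD 0 to 0.8 points.

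**Step 3: what adjustment can recover.** Six schools give 5 between-school degrees of freedom (df).

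- Arm + city: 6 − 4 = 2 residual df, t = 4.30.
- Arm + city + SES, where at least one pair is discordant: 6 − 5 = 1 residual df, t = 12.71. At the same residual SD, the arm interval is 3.1 to 3.6 times wider when the counts differ by one school and 5.1 times wider when they differ by two. When all three pairs are discordant in the same direction, SES and arm are aliased (probability 2[p(1−p)]³, which is 0.03 at *p* = 0.5).
- Arm + SES without city: 3 residual df. The interval is 1.2 to 1.6 times wider than with arm alone.
- Full list in section 6: five school-level variables (enrolment, SES, engagement, cycling-lane length, racks), two city-level variables (density, income) and weather, against the 4 df left after arm. School name alone takes all 5 df and is aliased with arm.

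**Step 4: effect of matching.** If both schools of a city share a class, the counts cannot differ, so P(differ) = 0. SES is then constant within city and costs no df beyond city.

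**The case against.** The strongest objection is the baseline measurement. All pupils are assessed before and after, and section 6 plans a regression on the change. A stable gap in level between high- and low-SES schools cancels in that model. This stands. A reader might infer that any SES difference passes straight into the estimated effect, or that the effect could never be told apart from a neighbourhood difference; the planned change model does not support that. What remains is SES-dependent response or trend, and any analysis that does not use baseline. The documents give no size for either.

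Allocation is random, so this is imprecision from chance imbalance and not confounding in expectation. That also stands.

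A reader might also set the 4.1-point illustration against the odds ratio of 1.5 in section 2.3.3. The comparison is not supported, because the protocol attaches that odds ratio to physical activity and not to ACS. For cycling, which the introduction puts below 2%, a 10-point gap would not be credible.

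To say that SES cannot be adjusted for at all would be too strong. SES on its own can be fitted unless it is aliased with arm, and family income and parental education give pupil-level information without using school df. The adjustment is unreliable rather than impossible.

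Finally, SES is one of several candidates for matching, and cycling-lane length or racks could be argued for instead. That is a fair point of preference. SES has the practical advantage that the plan already defines it as a two-level class. Figures 2 and 3 are not shown, but the equal-likelihood statement in section 7 does not fit a hidden SES match.

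**Conclusion.** The point holds as an avoidable weakness in the selection rule. With city as the only balancing factor, the arms will contain different numbers of high-SES schools with probability of about 0.58 to 0.69, and differ by two or more with probability 0.11 to 0.22, if 20–80% of schools are high SES. That share is assumed; the first probability stays above one half for shares from roughly 15% to 85%.

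The consequence is chance imbalance. Its effect on a change-score analysis depends on how far response or trend differs by SES, which the protocol does not quantify and which may be small. The df count does not depend on the assumed share: once a pair is discordant, arm, city and SES leave one between-school df, and the full covariate list is not estimable with six schools. The imbalance is therefore better prevented at selection than repaired in the analysis.

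**What to change.** In section 2.3.1, add a selection rule:

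1. Class schools as high or low SES with the GIS rule of section 4.2.2 as they come up on the random ordered list.
2. In each city take the first eligible school and pair it with the next eligible school of the same class.
3. Randomise arm within the pair.
4. Replace a school that declines by the next of the same class, or by the next on the list if that class is exhausted. The same rule can cover a school that proves ineligible after approach, for example on the number of consents.

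**Cost.** A little GIS desk work moved ahead of approach, a few sentences of protocol text, and some listed schools skipped. The trial is already paired by city, so no df are lost.

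The equal-chance aim of section 7 is largely kept. In a city with N schools and m in a given class (m ≥ 2), before refusals a school is drawn first with probability 1/N and second with probability [(m−1)/N]·[1/(m−1)] = 1/N. The total of 2/N is the same as under the present rule.
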